# Acetyl-L-carnitine (ALCAR) to enhance nerve regeneration in carpal tunnel syndrome: study protocol for a randomized, placebo-controlled trial

**DOI:** 10.1186/s13063-016-1324-2

**Published:** 2016-04-14

**Keywords:** Carpal tunnel syndrome, Peripheral nerve injury, Acetyl-L-carnitine, Motor unit number estimation, Nerve regeneration

## Abstract

**Background:**

Carpal tunnel syndrome (CTS) is the most common form of peripheral nerve injury, affecting approximately 3 % of the population. While surgery is effective in mild and moderate cases, nerve and functional recovery are often not complete in severe cases. Therefore, there is a need for adjuvant methods to improve nerve regeneration in those cases. Acetyl-L-carnitine (ALCAR) is involved in lipid transport, vital for mitochondrial function. Although it has been shown to be effective in various forms of neuropathies, it has not been used in traumatic or compressive peripheral nerve injury.

**Methods:**

In this pilot study we will utilize a double-blind, randomized, placebo-controlled design. Inclusion criteria will include adult patients with severe CTS. This will be confirmed by nerve conduction studies and motor unit number estimation (MUNE). Only those with severe motor unit loss in the thenar muscles (2 standard deviations [SD] below the mean for the age group) will be included. Eligible patients will be randomized to receive 3,000 mg/day of ALCAR orally or placebo following carpal tunnel release surgery for 2 months. The primary outcome will be MUNE with supplementary secondary outcome measures that include: 1) two-point discrimination; 2) Semmes-Weinstein monofilaments for pressure sensitivity; 3) cold and pain threshold for small fiber function; 4) Boston self-assessment Carpal Tunnel Questionnaire and 5) Disabilities of the Arm, Shoulder and Hand (DASH) questionnaire for symptom severity; and 6) Purdue Pegboard Test for hand functional performance. To follow post treatment recovery and monitor safety, patients will be seen at 3 months, 6 months and 1 year. The outcome measures will be analyzed using two-way ANOVA, with treatment assignment and time points being the independent factors. If significant associations are detected, a post hoc analysis will be completed. We aim to recruit ten patients into each of the two groups. Data from this pilot will provide the basis for power calculation for a full-scale trial.

**Discussion:**

ALCAR is a physiologic peptide crucial for fatty acid transport. ALCAR has been shown to be effective in neuroprotection in the central nervous system and increase peripheral nerve regeneration. This has been applied clinically to various systemic peripheral neuropathies including diabetic neuropathy, antiretroviral toxic neuropathy, and chemotherapy-induced peripheral neuropathy. While animal evidence exists for the benefit of ALCAR in compression neuropathy, there have been no human studies to date. This trial will represent the first use of ALCAR in peripheral nerve injury/compression neuropathy.

**Trial registration:**

NCT02141035; 20 April 2015

## Background

Carpal tunnel syndrome (CTS) is the most common peripheral nerve injury. Based on the clinical assessment of 3,000 randomly chosen individuals in Sweden, the prevalence of confirmed CTS was almost 3 % in the general population [1]. Of those, 25 % had severe symptoms and nerve injury that could not be sufficiently managed through conservative means [2]. The large number of afflicted individuals poses a major healthcare cost and social economic burden [3]. Indeed, it is estimated that up to half a million patients undergo surgery for CTS each year in the United States with an associated healthcare cost that exceeds $2 billion [4]. Therefore, much effort has been spent on attempts to improve treatment outcomes. Although conservative measures such as wrist splinting can be effective in milder cases, surgery is needed to relieve pressure on the median nerve when conservative measures fail. However, even with surgery, the outcome in more severe cases in which substantial axonal degeneration has already occurred remains poor [5]. One major reason is that even though injured nerve fibers have an inherent ability to regenerate, the regeneration proceeds very slowly with rates of only 1 mm/day in ideal circumstances [6, 7]. The regenerative capacity of axons and the Schwann cell (SC) growth support decline with time and distance from injury [8, 9].

To improve the speed and extent of nerve regeneration, novel treatment strategies are being explored. While decompression surgery is useful in alleviating further mechanical injury to the median nerve, it does little to influence the underlying molecular mechanisms of peripheral nerve regeneration. Although a number of potential therapeutic agents including FK506 [10], geldanamycin [11] and fibroblast growth factor [12] have been studied, their safety and tolerability for human application have challenges. In contrast, acetyl-L-carnitine (ALCAR) has an excellent safety track record for human use. It is a naturally occurring molecule that acts as an acetyl donor group that is critical for lipid transport and the maintaining of mitochondrial function. In vitro studies showed that ALCAR promoted cerebellar neuronal maturation and increased peripheral nerve regeneration in animal studies [13]. These findings prompted the evaluation of ALCAR in various neuropathies to improve nerve regeneration. Clinical conditions studied include antiretroviral toxic neuropathy [14], diabetic neuropathy [15] and chemotherapy-induced neuropathy [16]. Those studies showed that patients treated with ALCAR have less pain and better motor and sensory function. While this data is encouraging, the use of ALCAR in patients with compressive neuropathies remains largely untested. In an animal study, Kotil et al. found histopathological evidence of improvement when ALCAR was administered on its own or with concomitant decompression surgery [17]. The only human study to date that includes compression neuropathies was primarily designed to examine the tolerability of ALCAR [18]. However, evidence of nerve regeneration was not a primary objective of that study.

### Objective

The objective of the trial is to determine the efficacy of ALCAR on nerve regeneration in patients with severe CTS.

### Hypothesis

ALCAR will significantly increase motor axonal regeneration, improve sensory function and more rapidly resolve CTS symptoms.

## Methods

### Basic trial design

This double-blinded, placebo-controlled trial has received ethics approval from the University of Alberta Health Ethics Research Board (Pro00045538). The study protocol has been reviewed by Health Canada, and a No Objection Letter (NOL) has been issued for the use of ALCAR. Subjects will be recruited from plastic surgery clinics at the University of Alberta Hospital and Royal Alexandra Hospital as well as the electromyography (EMG) clinic at the Glenrose Rehabilitation Hospital.

### Subjects

All patients referred to either the plastic surgery clinics or the EMG lab will be eligible to be screened. Inclusion into the study will be based upon the criteria listed in Table 1. Patients meeting eligibility criteria will be recruited and informed consent will be obtained. They will then undergo motor unit number estimation (MUNE) to quantify the severity of motor axonal loss. Only those with motor axonal loss of > 2 SD below the mean for the age group will be included in the study.

**Table 1 Tab1:** Inclusion and exclusion criteria for patient selection

Inclusion criteria	Exclusion criteria
1) Age > 18 years	1) Motor unit loss in the median nerve less than 2 standard deviations below the mean for the age group
2) One or more of the following symptoms of CTS	2) Presence of other neurologic conditions
a) Numbness and paresthesias in the median nerve distributions	3) Previous carpal tunnel release
b) Precipitation of those symptoms by repetitive motions that are relieved by rubbing and/or shaking	4) Cognitive impairment that renders the patient incapable of providing consent
c) Nocturnal awakening of the above symptoms	5) History of seizures
d) Weakness of thumb abduction and thenar atrophy	6) Kidney disease/renal impairment
	7) Sensitivity to any of the drug components of the formulation or are
	8) Pregnant/breast feeding
	9) For women of child-bearing potential, those that are not willing to use adequate contraceptive prevention methods for at least 30 days after the last dose of the medication.

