### Primary outcome

The primary endpoint will be motor axon reinnervation in the thenar muscles. This will be done using MUNE, a non-invasive electrophysiological technique. Initially introduced in the 1970s [19, 20], multipoint stimulation, the most commonly used MUNE technique, has been shown to be a reliable test for measuring motor axon reinnervation [5]. Apart from providing an objective assessment of large myelinated nerve fibers, MUNE will also serve as a screening tool for eligibility for the trial. To quantify treatment response, MUNE will be repeated at 3, 6 and 12 months post-operatively.

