### Secondary outcomes

Secondary outcomes of the study focus on sensory function restoration and functional outcomes. Measures will include:Two-point discrimination (Aβ fibers) using Dellon-MacKinnon DiskPressure sensitivity (Aβ fibers) using Semmes-Weinstein monofilamentCold threshold (Aδ fibers) and pain threshold (C fibers) using CASE IV quantitative sensory testing (QST) equipmentBoston CTS Questionnaire to monitor symptom severityDisabilities of the Arm, Shoulder and Hand (DASH) questionnaire for functional outcomesMoberg Pick-up Test to measure hand dexterity and functional performance

All outcome measures will be monitored at baseline, 3 months, 6 months and 12 months. Sensory testing of peripheral nerves provides more of a challenge, given the multiple fiber types that provide sensory feedback. The above list of tests is designed to capture the full range of sensory fiber functions. A major advantage of QST is that it provides an objective means of measuring the function of different classes of nerve fibers with good reliability. The DASH and the Boston questionnaires used to evaluate symptom severity are both well validated in CTS [21]. Finally, to objectively measure hand functional performance, the Moberg Pick-up Test is a validated tool for CTS with good reliability [22]. All primary and secondary outcome measures will be performed by the same investigators (MC, KMC). To verify the inter-rater reliability of these tests, a subset of patients will undergo separate assessment by two investigators independently in a blinded manner.

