### Sample size

Initially, a pilot study of 20 patients will be carried out. Evaluation of the effect size will be based on the primary outcome MUNE. This will provide the necessary data for the sample size calculation for a fully powered large-scale study.

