### Statistical analysis

Demographic data will be compiled and analyzed for differences using a Student’s *t*-test and Fisher’s exact test. The primary and secondary outcome measures will be analyzed using two-way ANOVA with the treatment groups and time points being the independent factors. If significant associations are detected, a post hoc analysis will be done for pairwise comparisons. Due to the exploratory nature of the study, sample size calculations and formal analysis of missing data will not be undertaken.

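### MUNE is range-restricted at entry and is also the primary outcome, but the planned two-way ANOVA has one residual variance for all visits, which need not fit the 12-month comparison or the full-scale sample size

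*Protocol article*

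**What the plan says.** Four statements in the Protocol article bear on this.

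- **Entry (Subjects; Table 1 gives the mirror-image exclusion).** "Only those with motor axonal loss of > 2 SD below the mean for the age group will be included in the study".
- **Same measure as outcome (Primary outcome).** The endpoint is motor reinnervation measured by MUNE, and "MUNE will also serve as a screening tool for eligibility for the trial". After surgery, "MUNE will be repeated at 3, 6 and 12 months post-operatively". The Secondary outcomes section adds: "All outcome measures will be monitored at baseline, 3 months, 6 months and 12 months".
- **Model (Statistical analysis).** "The primary and secondary outcome measures will be analyzed using two-way ANOVA with the treatment groups and time points being the independent factors". Then: "If significant associations are detected, a post hoc analysis will be done for pairwise comparisons".
- **Use of the result (Sample size).** The effect size is to be judged on MUNE in 20 patients, and "This will provide the necessary data for the sample size calculation for a fully powered large-scale study".

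The text names no baseline covariate and no variance that differs by visit. It does not say whether baseline is a level of the time factor, which error term the pairwise tests use, or which SD goes forward to the larger trial. It gives no MUNE SD, normative or by visit.

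**The concern.** A cap on the outcome at entry narrows its spread at that visit. The cap does not apply after surgery. If patients then recover to different degrees, MUNE spreads out over follow-up. A standard two-way ANOVA averages the variances of all visits into one mean square and uses it for every comparison. If the baseline and early visits are the tighter ones, that average is too small for the 12-month comparison.

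Two things are at stake. One is the false-positive rate of the late between-arm comparisons. The other is the variability estimate for the full-scale trial. The Limitations section says no prior data on effect size and variability exist in this condition, so supplying them is a main purpose of the pilot.

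This is separate from within-patient correlation. A patient term that keeps a common variance still uses one error variance for visits whose spread may differ.

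**Working it through.** **Inputs.** From the Protocol article: 20 patients, 10 per arm; visits at baseline, 3, 6 and 12 months; two-way ANOVA; the entry rule. The 20 rests on no stated effect size, SD, alpha or power, so there is no figure of the plan to reproduce. Assumed here: two-sided 5%, 80% power, within-patient correlation 0.6, and the visit SDs below.

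**Step 1: what the entry rule does alone.** Work in age-norm SD units, with a screened population of SD 1 cut at -2.
- Centred at -2, the truncated SD is sqrt(1 - 2/π) = 0.60, so the untruncated SD is 1/0.60 = 1.66 times larger. Centred at -3 the ratio is 1.26, and at -4 it is 1.06.
- The same selected patients are followed, so the relevant follow-up variance is ρ² × (truncated variance) + 1 - ρ², where ρ is the baseline-to-follow-up correlation before selection. Centred at -2 with ρ = 0.6: 0.36 × 0.363 + 0.64 = 0.771, SD 0.878, ratio 0.878/0.603 = 1.46. With ρ = 0.8 or 0.9 the ratio is 1.28 or 1.15. Centred at -3 the three ratios are 1.17, 1.10 and 1.05.
- If the SD steps up once by a ratio r and stays there, pooled variance / 12-month variance = (1 + 3r²)/(4r²). For r = 1.46 this is (1 + 6.39)/8.53 = 0.87, and the standard-error (SE) ratio is √0.87 = 0.93. For r = 1.05 it is (1 + 3.31)/4.41 = 0.98, and the SE ratio is 0.99.

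Truncation alone therefore understates the 12-month SE by about 1% to 7%. A simulation of the entry rule with measurement error gave the same range.

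**Step 2: adding varied recovery.** In that simulation, an SD of individual gain of 0.5 to 1.0 normative SD gave SE ratios of 0.75 to 0.93. Recovery proportional to the initial deficit gave 0.84 to 1.36, so the pooled SE can also be too large.

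**Step 3: error rate at 12 months.** Pooled variance is the mean of the four visit variances. For example, (1 + 1.44 + 1.82 + 2.25)/4 = 1.63, and 1.63/2.25 = 0.72. The type I error is for an ungated between-arm test at 12 months with pooled error on 72 degrees of freedom (40,000 runs).

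| Assumed SDs (0, 3, 6, 12 months) | Pooled / 12-month variance | SE ratio | Type I error |
|---|---|---|---|
| 1, 1.2, 1.35, 1.5 | 0.72 | 0.85 | 10% |
| 1, 1.33, 1.67, 2 | 0.60 | 0.77 | 13% |
| 1, 1.5, 1.5, 1.5 | 0.86 | 0.93 | 7% |
| 1.25, 1.17, 1.08, 1 | 1.27 | 1.13 | 3% |

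Using the 12-month variance alone gives about 5% throughout.

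**Step 4: the stated gate.** The pairwise tests follow only a significant result. Requiring p < 0.05 for treatment or interaction first lowers the first two rows to about 8% and 11% when visits are treated as independent. With a patient term as well, they fall to about 5% and 7%.

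**Step 5: without baseline as a time level.** The first two rows become 82% of the 12-month variance with 8% error, and 71% with 10% (ungated). A constant post-operative SD gives no error.

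**Step 6: if a pooled mean square were carried forward.** For a difference of 0.5 SD at 80% power, 63.8 (64) per arm are needed. At 0.72 of the true variance, 63.8 × 0.72 = 46 per arm and true power is about 66%. At 0.60, 63.8 × 0.60 = 38 per arm and power is about 58%.

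**The case against.** The strongest reply is that the direction is assumed. With no SD at any visit in the protocol, nobody can say that the pooled error is too small. The entry rule contributes little by itself, less still if most patients lie well below the cut-off, and recovery proportional to the deficit turns the sign. This stands. A reader might infer that the 12-month standard error will be too small because of the entry rule, and the documents do not support that.

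The ungated error rates are also not those of the stated procedure. The gate lowers them. Combined with a patient term it brings them near 5% to 7%, and an added Bonferroni factor of 4 for the visits gives at most 5.3%. This stands too, although the article states neither a patient term nor a multiplicity adjustment.

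Baseline as a time level is an inference from the visit schedule, since the Primary outcome section ties treatment response to the three post-operative visits. A reader might also infer that the full-scale trial will be undersized. No passage says the pooled mean square will be used for it, and the pilot yields each visit's SD directly. Step 6 is therefore only a warning about one possible choice.

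The last reply is that covariance structure and error terms belong in an analysis plan that is not shown. That excuses their absence. It does not cover a model the article names and whose standard form has a common variance. The exploratory label excuses low power, but not a poor variance estimate from a study meant to supply one.

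**Conclusion.** The point holds in conditional form. The plan fixes a common-variance ANOVA on an outcome that is range-restricted at entry, and the pooled error need not fit any particular visit. If baseline is a time level and SDs rise from 1 to 1.5 or from 1 to 2, the 12-month test has about 10% or 13% error ungated, about 8% or 11% with the protocol's gate, and about 5% or 7% with a patient term as well. If SDs fall, the test is conservative at about 3%. The SD patterns, the correlation of 0.6 and the place of baseline in the model are all assumptions.

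Varied recovery drives most of any understatement, and truncation a small part. Treating visits as independent is a separate and larger matter: at correlation 0.6 and equal variances, the treatment main effect then has about 24% error. The remedy below does not depend on which way the variance moves.

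**What to change.** In Statistical analysis, replace the two-way ANOVA for MUNE with an analysis of the 3-, 6- and 12-month values that takes baseline MUNE as a covariate and not as a time level. Use either a mixed model with unstructured covariance over the three visits or an ANCOVA at each visit, so that each comparison uses its own visit's variance.

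In Sample size, state that the full-scale calculation will use the residual SD, with its confidence interval, at the follow-up visit chosen as that trial's endpoint, and not a mean square pooled over visits.

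The change is to wording only. Error degrees of freedom for one comparison fall from 72 (80 observations less 8 cell means) to 18 (20 less 2), or 17 with the covariate. The critical t rises from 1.99 to about 2.10, so intervals widen by about 5.5% for the same SD (2.10/1.99 = 1.055). No visit or measurement is added.

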### Randomization

After enrollment, patients will be randomized to placebo or ALCAR. A randomization sequence will be generated electronically and kept by a statistician not directly involved in patient care. Randomization will be kept on a computer under password encryption. The randomization code will only be broken if a patient experiences a severe adverse event. At the end of the study the statistician will provide the research team with the randomization codes.

### Blinding

The study will be administered in a double-blind manner. The randomization sequence will be kept confidential and only accessible to authorized personnel. The pharmacy will distribute identical pills in bottles labeled with A or B. The research team will be unaware of which contains the study drug or placebo. This will be maintained until the final follow-up has occurred, at which point the research team will be unblinded.

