### Interventions

Patients will be assigned to either the placebo or ALCAR arm of the study. Both placebo and ALCAR will be fabricated by the same pharmaceutical company (Sigma-Tau, Rome, Italy). They are identical in appearance and taste. Upon arrival, the tablets will be packaged by the pharmacy into identical boxes labeled with a random sequence code. Both groups will undergo open carpal tunnel release without epineurolysis performed by experienced hand surgeons (JO, MM). Post-operatively, patients will take the medications for 2 months. Patients randomized to the ALCAR arm will take 3,000 mg orally divided in three times per day dosing, while the control group will take a matched placebo. The dosing schedule for the study drug was chosen based on previous work by Bianchi et al. (2005) that showed good tolerability and efficacy [23].

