### Safety and potential risks

To monitor any potential adverse events, rigorous safety measures have been put in place to ensure patient safety. Initial baseline testing will include:Physical examinationVitalsEKGUrine pregnancy testsComplete blood count with differential, electrolytes (Na, K, Cl, CO_2_), creatinine, urea, alanine aminotransferase, aspartate aminotransferase, alkaline phosphatase and bilirubinSerum ALCAR

Vital signs (blood pressure, temperature, pulse, respiratory rate, oxygen saturation) will be recorded at every visit. Safety lab tests including blood chemistries will be done at screening, and periodically during follow-up visits. In addition, an electrocardiogram will be done at screening. The serum ALCAR level will also be monitored. In healthy subjects, the serum ALCAR levels had a range of 10–70 μmol/L with a mean of 39 μmol/L. In a large study of over 333 patients with diabetic neuropathy taking 3 g of ALCAR/day (the same dose used in this study), the rise in serum level was only around 50 % compared to baseline. Since no sign of ALCAR toxicity was observed in any of the subjects, we anticipate that the chances of toxic effects in this study will be very small.

All adverse events will be documented at follow-up visits. Further laboratory investigations will be done depending on the nature and severity of the adverse events reported.

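### Bottles labelled A or B are an arm-level code that conflicts with the random sequence code on the boxes, so one code break could reveal the allocation of up to all 20 patients

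*Protocol article*

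**What the plan says.** The protocol article describes the labelling of trial supplies twice.

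- Blinding: "The pharmacy will distribute identical pills in bottles labeled with A or B". The next sentence adds: "The research team will be unaware of which contains the study drug or placebo".
- Interventions: "the tablets will be packaged by the pharmacy into identical boxes labeled with a random sequence code".

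On breaking the code, the Randomization section says: "The randomization code will only be broken if a patient experiences a severe adverse event". It places the sequence with a statistician who has no direct part in patient care.

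On size, the Sample size section says "Initially, a pilot study of 20 patients will be carried out", and the Methods part of the abstract says "We aim to recruit ten patients into each of the two groups".

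The Secondary outcomes section assigns all primary and secondary measurements to the same two investigators, with visits at baseline, 3, 6 and 12 months. From the Trial management section, these are the principal investigator and the person assisting in running the trial.

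**The concern.** A two-letter label sorts the patients into their treatment groups from the first bottle. The blind then rests on a single fact, namely which letter is the drug. Once that is known for one patient, it is known for everyone with a visible letter, including patients enrolled later as soon as they receive a bottle. The article foresees an event that could release this fact, a code break during the trial, and describes no way to unblind one patient without decoding the letters.

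MUNE and the sensory tests are carried out by the assessors, and the Boston and DASH questionnaires are self-reported. All of them depend on the blind, and the Strengths section offers the double-blind design as the protection against bias. The Sample size section says the MUNE effect size from this pilot will be used to plan the full-scale trial. A loss of blinding could therefore distort that planning figure, and it cannot be repaired afterwards.

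**Working it through.** **Inputs**

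- Patients: 2 groups × 10 = 20 (abstract), which agrees with the 20 in the Sample size section.
- Labels: two letters (Blinding), or a random sequence code (Interventions).
- Code break: allowed after a severe adverse event in one patient (Randomization).
- MUNE visits after baseline: 3 per patient, at 3, 6 and 12 months (Primary outcome).

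**Step 1. Is the letter an arm-level code?** The Blinding section says the team does not know which label contains drug and which placebo. That makes sense only if one letter stands for each arm. The article mentions no other label on the bottle.

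**Step 2. Can the two descriptions both be true?** Both container and label differ: bottles with A or B, and boxes with a random sequence code. There are three readings.

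1. The patient receives only a lettered bottle. The Interventions sentence is then wrong, and the arm letter is visible.
2. A lettered bottle sits inside a coded box. Both sentences can stand, but anyone who sees the bottle still sees the arm letter.
3. The only visible label is a code unique to each patient. The risk disappears, but the Blinding sentence is then wrong. The article also does not say that the random sequence code is unique to each patient.

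Under every reading, either a sentence is wrong or the arm letter can be seen.

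**Step 3. What does one code break reveal?** Let k be the number of other patients whose letter is known to the person who learns the code, with k from 0 to 19. With two letters, decoding one fixes the other.

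| Labelling | Allocations revealed by one break | Range |
|---|---|---|
| A/B letters | 1 + k | 1 to 20 of 20 |
| Unique code per patient | 1 | 1 of 20 |

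**Step 4. How many primary measurements could be exposed?** The trial plans 20 × 3 = 60 MUNE assessments after baseline. The ceiling is reached if the code is broken before any 3-month visit, all letters are or become known, and the information reaches the assessors. In that case all 60 could be done without the blind, against 1 × 3 = 3 under patient-level codes. A later break, or fewer known letters, exposes fewer.

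**The case against.** **The article is a summary.** Kit numbering and emergency unblinding are commonly left to a full protocol, which is not shown, and a lettered bottle inside a coded box would fit both sentences. This stands as a caution about what is done in practice. It does not remove the point, which rests on what the article states: an arm-level letter in one section and a different label in another. The box-and-bottle reading also leaves the letter visible on the bottle.

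**All 20 is a worst case.** This stands. The person who learns the code must also know the letters, and the assessors are affected only if they are that person or are told. The article provides several separations: the sequence is held by the statistician, access is restricted, a research pharmacy handles the drug, a safety board manages adverse events, and data entry is kept apart from the investigators who see patients. These reduce the risk. None of them says that a code break is kept from the assessors.

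**Stronger readings that the documents do not support**

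- *A probability of full unblinding.* The article gives no rate of severe adverse events. Its rule limits when the code may be broken and does not clearly require a break after each such event. Any percentage would rest on invented inputs.
- *Unblinding by one serum ALCAR result.* The Safety section says "The serum ALCAR level will also be monitored". It gives an untreated mean of 39 μmol/L, a range of 10–70, and a rise of about 50% on this dose. That gives 39 × 1.5 = 58.5, inside the untreated range, so one value would rarely identify the arm. Treatment lasts 2 months and the first listed follow-up is at 3 months. No on-treatment draw, and no disclosure of results to assessors, is stated.
- *Guessing the next assignment.* Ten per group is an aim. No blocking or forced balance is described.
- *Bias from the timing of final unblinding.* The Blinding section says "This will be maintained until the final follow-up has occurred, at which point the research team will be unblinded". That comes after all visits and cannot affect the visit measurements.

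**It is an exploratory pilot.** True, and no stated sample size, significance level or power figure changes. The blind still protects the MUNE effect estimate that the pilot is meant to supply.

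**Conclusion.** The point holds in a limited form. The Blinding and Interventions sections describe different labels and must be reconciled, together with the code-break rule in the Randomization section. If the dispensed bottle shows the arm letter, one break reveals between 1 and 20 of the 20 allocations, depending on how many letters are known to the person who learns the code. Patient-level codes would hold this to 1.

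This rests on two assumptions: that A and B each denote one arm, as the Blinding section implies, and that staff can see the bottle label. Harm to the outcome data further requires that the decoded information reaches the two investigators who do the assessments. The article neither says that it would nor rules it out. It gives no basis for how likely a break is, so the exposure can be stated but its probability cannot.

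**What to change.** - **Blinding:** delete the sentence on bottles labelled A or B. State that each patient receives a uniquely numbered kit, and that bottle and box carry the same number and no arm-level mark.
- **Interventions:** replace the random sequence code wording with the same kit description.
- **Randomization:** state that the kit-to-treatment list is held only by the pharmacy and the independent statistician, that any code break is for a single patient, and that the result is not disclosed to the outcome assessors where avoidable. When the code may be broken is a matter for the investigators and is not touched here.

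**Cost:** about twenty labels and aligned wording in three sections. The pharmacy already repackages the tablets. The Trial status section says recruitment is under way, so stock already prepared may need relabelling. For any patient who has already received a lettered bottle the change comes too late to hide the letter, and the key to the letters should be kept from the assessors.
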